### Secondary outcome measurement

2.14

The scores change of clinical scales will be the secondary outcome measurement. First is NIHSS (National Institutes of Health Stroke Scale), which is a standardized scale to describe neurological deficits in stroke patients. Fugl-Meyer Assessment is usually used to evaluate motor function. It includes an assessment of the upper extremity and lower extremity. This study tends to emphasize the patients’ gait, so we selected the part of the lower limbs only, with a total score of 34. Most patients with post-stroke hemiplegia have trouble in balance control; Berg Balance Scale was developed as a tool for quantifying the ability of keeping balance. Barthel Index, Modified Rankin Scale, and Stroke-specific Quality of Life Scale indicate the capacity of daily living.

### Incidence of AEs

2.15

Any related and unexpected AEs happened during this study will be recorded in detail, and the occurrence of these will be analyzed. Serious AEs will be reported to the chief investigator, CTG, and REC immediately. They will make decision on whether the participant needs to withdraw from the trial or the study should be adjusted. Those who suffer accidental injury from our trial will be provided free treatment until they recover.

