### Randomization and allocation concealment

2.8

All participants will be assigned to experimental group or control group in a 1:1 ratio according to a computer-generated randomization list by an independent researcher. In accordance with best practice recommendations for randomized controlled trials, allocation concealment will be employed. Assignments will be sealed in opaque envelopes by a nurse who will be trained before the trial and will not participate in treatment. As only the therapist who opens the envelopes will assign patients to a different group. It is impossible to predict and interference the assignments factitiously. The participants will be blinded. They will be told that they have been randomly allocated to one group, and be treated with regular rehabilitation therapies. Moreover, the outcome assessors and data statistical analysts will remain blinded to the intervention methods. Unblinding will be considered when adverse events (AEs) occur.

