**Figure 3 F3:**
[figure not shown]
Intradermal needles (sham: left, authentic: right).

The intradermal needles (0.2 × 1.5 mm, Seirin, Japan) (Fig. 2) are disposable and sterile, with waterproof adhesive tape above which can help to affix the needle beneath. Patients after modern rehabilitation training will be inserted with these needles in a perpendicular fashion. In comparison to typical traditional acupuncture, intradermal needles are smaller, less deeply, and with less manipulation. All needles will be replaced after treatment the next day. In other words, patients will carry these intradermal needles for the whole course of therapy. The intradermal needle treatment will be implemented once a day from Monday to Friday, lasting 4 weeks. To ensure the optimal effects of needle stimulation, our therapists will be required to have clinical experience of acupuncture treatments for at least 8 years. The items are presented in the Standards for Reporting Interventions in Clinical Trials of Acupuncture (STRICTA).^[29]^

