#### Control group

2.9.2

Patients allocated to the control group will receive conventional rehabilitation programs for post-stroke hemiplegia. Therapies are based on neurodevelopmental theory and will include position of limb, passive and active assisted activities, postural balance training, trunk controlling, task oriented practicing, among others.^[30]^ It will last approximately 1 hour every time. After this treatment, sham intradermal needles, which look similar at the surface but without needle underneath will be used. It can be adhered to the skin instead of being needle-inserted. The acupoints location and manipulations are taken equally with experimental group. The retention time and frequency are identical to authentic intradermal needle therapy. To ensure the homogeneity of research, all rehabilitation programs will be done by qualified therapists and we have trained them with rehabilitation technology before the implementation of the project (Fig. 1).

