### Follow up

2.10

After finishing the treatment of four weeks, follow-up will be done on all patients for three months. Because of the specificity of stroke patients’ recovery, they may accept other rehabilitation treatments during this period. Considering the ethical issue, we will not intervene in this except for the prohibition of additional intradermal needle. We have created rehabilitation diaries and telephone interview forms (TIFs). We will train and ask each patient to record their condition every day after hospital discharge, such as medication used, method and frequency of treatment, AEs, and so on. At the end of each month, our assessors will call patients to enquire their conditions based on the TIFs. At the end of follow-up, participants will be referred for RSSCAN gait system and clinical scales as before. All forms will be collected by the data collectors regardless whether they have withdrawn from the trial assessments for reviewing at the end of this trial.

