### Data management and monitoring

2.16

Before the study, we have set up Data Management and Monitoring Committee (DMC) and trained all researchers about data management. DMC is independent from trial investigators, and has no competing interests. First, all assessors will be responsible for the assessment and acquisition of participants’ information during the study. After they finish the Case Report Forms and TIFs completely, 2 data collectors will convert these and rehabilitation dairies to electronic data. All these original data related to the research including paper forms and electronic documents will be archived securely in the Clinical Research Center of Dongzhimen Hospital. Only researchers in our study team will have access to the final complete data, others who have any questions will be required written requests to our data manager to be permitted.

Monitoring is another role and responsibility of DMC. Members of DMC will monitor the overall quality and completeness of the data, examine original documents, interview assessors, and confirm that the study is complied with the principles of this protocol. The monitors will verify that all AEs be recorded in the correct format.

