## Discussion

3

Hemiplegia is the most common symptom of stroke. The typical feature of this disease is that the apraxia will exist and continue for several weeks, months, or years. It causes a heavy burden on both healthcare resources and the society. Cohort studies have consistently reinforced the importance of post-stroke rehabilitation to stimulate recovery.^[34]^ Acupuncture is considered as a frequently used therapy to harmonize and regulate the functional activities of the brain and body. Previous studies have indicated that acupuncture combined with conventional rehabilitation therapies is more effective for post-stroke patients.^[35]^ However, the treatment of acupuncture is carried out at clinic, lasting temporarily. Patients cannot receive any therapeutic measures besides this period. Thus, therapies that can maintain for longer time are required.

Intradermal needle, with the advantages of convenience, little pain, long-lasting, satisfactory effects, and few adverse reactions, is attracting increasing clinical attention.^[36]^ It is inserted and affixed in superficial skin, which is densely packed with sensory and motor neurons. The nerves of skin are associated with brain. It can be transmitted to central nervous system when someone stimulates the acupoints on the skin. The cerebral center integrates the information and corresponds through homologous movement.^[37]^ In the aspect of different needle-retaining, some researchers randomly divided 251 ischemic apoplexy patients into 20, 40, and 60-minute groups. Through the results of hemorheological values, the therapeutic effect of 60-minute group was the best.^[38]^ Intradermal needle is a kind of superficial needling, which can be maintained for 1–3 days, so as to extend the effect of acupuncture. It is therefore of great clinical significance that our study uses intradermal needle therapy to treat post-stroke hemiplegia.

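### Section 2.15 limits AE recording and analysis to related and unexpected events, conflicts with sections 2.10 and 2.16, and could leave foreseeable needle-site reactions out of the incidence

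*Protocol article*

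**What the plan says.** Section 2.15 (Incidence of AEs) gives the rule: "Any related and unexpected AEs happened during this study will be recorded in detail, and the occurrence of these will be analyzed". The second half of that sentence makes the filtered set the analysis set, and no other section says which AEs are analysed. Serious events have a separate reporting rule without the filter: "Serious AEs will be reported to the chief investigator, CTG, and REC immediately".

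Two other sections are wider. In section 2.16 (Data management and monitoring), "The monitors will verify that all AEs be recorded in the correct format". In section 2.10 (Follow up), patients keep a diary in which they "record their condition every day after hospital discharge, such as medication used, method and frequency of treatment, AEs, and so on".

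On exposure, section 2.9.1 states that "patients will carry these intradermal needles for the whole course of therapy", while section 2.9.2 states that for controls "sham intradermal needles, which look similar at the surface but without needle underneath will be used". Section 2.8 adds that "Unblinding will be considered when adverse events (AEs) occur".

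**The concern.** A needle kept in the skin through a four-week course can be expected to cause some local reactions. Such a reaction is related to treatment but not unexpected, so it fails the literal test in section 2.15. An event judged unrelated, for example a fall, fails it too.

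The loss would not be even between arms. The sham can irritate the skin through its adhesive, but it cannot cause a needle reaction. A filter on expectedness therefore bears most on the harm most likely to differ between the arms.

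The filter also requires a judgement of relatedness before an event qualifies. Because an AE may prompt unblinding under section 2.8, that judgement could be made with the arm known. Recording first and classifying afterwards keeps the two steps apart.

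A pilot meant to inform a larger trial can usefully describe harms. That description is worth little if the main foreseeable harm can be excluded by definition.

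**Working it through.** **Inputs**
- Planned evaluable size: 20 per group, 40 in all (section 2.3).
- Drop-out: 20%; 25 per group, 50 in all, recruited (section 2.3).
- 95% confidence intervals and two-sided testing at 0.05 (section 2.18).
- Local-reaction rate: not given in the article. Assumed here as 10%, 20%, 30% or 40% of needle patients.

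**Step 1: the article's own figure.** The AE rule carries no number. The group sizes used below reproduce: 20/(1 − 0.20) = 25 per group and 40/(1 − 0.20) = 50 in all.

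**Step 2: what each reading keeps in the incidence**

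| Event | Literal reading (related *and* unexpected) | Inclusive reading (related *or* unexpected) |
|---|---|---|
| Related, unexpected | kept | kept |
| Related, expected (foreseeable needle-site reaction) | left out | kept |
| Unrelated, unexpected | left out | kept |
| Unrelated, expected | left out | left out |

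**Step 3: whether the other sections close the gap**
- Section 2.16 covers all AEs, but it concerns checking how they are recorded and does not change what is analysed.
- The diary in section 2.10 has no filter, but it is described for the time after discharge, within the follow-up section. It does not clearly cover the four weeks of needle wear.
- The serious-event rule in section 2.15 has no filter, but minor local reactions are not serious events.

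**Step 4: how many patients this could concern.** With n = 20 needle patients and true reaction rate p, the expected number affected is n × p and the chance of at least one is 1 − (1 − p)^20.

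| Assumed p | Expected affected of 20 | Chance of at least one | Count in the incidence if all are classed as expected |
|---|---|---|---|
| 10% | 2 | 88% | 0 |
| 20% | 4 | 99% | 0 |
| 30% | 6 | over 99% | 0 |
| 40% | 8 | over 99% | 0 |

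If only some of the reactions are classed as expected, the loss shrinks in proportion. With 25 per group the expected numbers are 2.5, 5, 7.5 and 10.

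**Step 5: what a reported zero would imply.** The exact two-sided 95% upper limit for 0 of n is 1 − 0.025^(1/n).
- n = 20: 1 − 0.025^(1/20) = 16.8%.
- n = 25: 1 − 0.025^(1/25) = 13.7%.

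Both limits lie below assumed true rates of 20%, 30% and 40%, so a zero produced by the filter would appear to rule those rates out. At 10% both limits still cover the true rate; the count would be wrong but the interval would not exclude the truth.

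**The case against.** The strongest reply is that the sentence is loosely written and not restrictive. It does not contain the word *only*, and it speaks of detailed recording, which does not say that other events go unrecorded. In an article with rough English it may mean related events and unexpected events, and needle-site reactions would then be kept. Sections 2.10 and 2.16 suggest that wide recording was intended. No section lists expected reactions, so it is an assumption that local reactions would be classed that way. The article is also a condensed account, and AE definitions and form fields are commonly left to the full protocol.

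Much of this stands, and it limits the point to what the rule could do. It does not remove the point. This is a stated rule and not an omitted detail, it is the only one that defines the analysis set, and the wider sections conflict with it without changing it. Even the inclusive reading drops events that are both unrelated and expected.

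Two stronger readings are not supported:
- A reader might infer that the treating therapist, who knows the arm, decides which events are recorded. No section gives the therapist that role. Section 2.16 makes the assessors responsible for acquiring participants' information, and section 2.8 keeps them blinded.
- A reader might infer that a formal safety comparison with sham would be falsely negative. Section 2.18 names no between-arm safety test, and the sham adhesive can cause skin reactions of its own. Full recording would also give little power at modest rates: for a two-sided Fisher test (chosen only for illustration) with 20 per arm and an assumed 5% sham rate, power is 2%, 17%, 45% and 72% at needle-arm rates of 10%, 20%, 30% and 40%. The case for full recording is description, not testing.

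**Conclusion.** The point holds as an internal conflict and a poorly chosen filter. Taken literally, section 2.15 keeps foreseeable needle-site reactions and events judged unrelated out of the AE incidence, and sections 2.10 and 2.16 point the other way without settling the matter. The pilot's safety description could therefore look cleaner than it is, mainly in the needle arm.

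The size rests on assumed reaction rates and on the reactions being classed as expected. On those terms about 2 to 8 of 20 needle patients could be left out, and a reported 0/20 or 0/25 would mislead. The documents do not show that reactions will in fact be missed, only that the rule as worded allows it.

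**What to change.** Reword section 2.15 so that all AEs in both arms, from first treatment to the end of follow-up, are recorded whatever their relatedness or expectedness. Each is then classified for seriousness, relatedness and expectedness, where possible by the assessors who are already blinded, and incidence is reported by arm. Bring section 2.10 into line so that AE capture clearly covers the treatment weeks as well as the time after discharge, and section 2.16 so that the monitors check the same set of events.

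The cost is a short amendment and a few more AE entries. No added patient procedures are needed.

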### Data management and monitoring

2.16

Before the study, we have set up Data Management and Monitoring Committee (DMC) and trained all researchers about data management. DMC is independent from trial investigators, and has no competing interests. First, all assessors will be responsible for the assessment and acquisition of participants’ information during the study. After they finish the Case Report Forms and TIFs completely, 2 data collectors will convert these and rehabilitation dairies to electronic data. All these original data related to the research including paper forms and electronic documents will be archived securely in the Clinical Research Center of Dongzhimen Hospital. Only researchers in our study team will have access to the final complete data, others who have any questions will be required written requests to our data manager to be permitted.

Monitoring is another role and responsibility of DMC. Members of DMC will monitor the overall quality and completeness of the data, examine original documents, interview assessors, and confirm that the study is complied with the principles of this protocol. The monitors will verify that all AEs be recorded in the correct format.

### Auditing

2.17

Research Department of Dongzhimen Hospital will in charge of auditing, which is independent form trial investigators. The processes reviewed include participant enrolment, consent, eligibility, allocation to study groups, adherence to trial interventions, policies to protect participants, completeness, accuracy, and timeliness of data collection. The periodic review is every 2 months.

### Statistical analysis

2.18

Statisticians will be responsible for the statistical analysis. The main analysis will compare the changes in all outcome measurements of between-group or within-group to evaluate the effect of intradermal needle treatment. An intention-to treat analysis will be conducted using the SPSS (Statistical Product and Service Solutions) program (version 22.0, Chicago, IL). Continuous variables will be expressed as means ± standard deviations, Wilcoxon rank sum tests with no adjustment for multiple comparisons will be used for comparisons. Categorical variables will be presented with frequencies or percentages. Fisher exact test will be applied in testing blinding between groups because of small cell counts. A *P* value of <.05 (2-sided) is considered to indicate statistical significance, with 95% confidence intervals.

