### Study design

2.1

This study is a prospective, single-centered, randomized, patient-assessor-blinded, parallel-controlled clinical trial. The chief investigator and Clinical Trials Group (CTG) will take responsibility for the overall management of this trial, including the study design, coordination, monitoring, data analysis and results reporting. Any changes to the study protocol will be submitted to them. They will decide whether it is necessary to change or even stop the protocol. We began this study after having discussed in its entirety with each member of the research team. The patients according to inclusive criteria of Dongzhimen Hospital will be recruited and then invited to participate in this study. The eligible participants will be randomly allocated into two groups by a 1:1 ratio using a randomization procedure. All patients will receive conventional rehabilitation therapies. On top of basic treatment, the experimental group will receive authentic intradermal needling, whereas the control group will receive sham intradermal needling. All therapeutic methods will be taken once a day, 5 days per week. This study is designed to coincide with routine care as much as possible and align with follow-up visits. After 4 weeks of treatment and 3-month follow-up, we will evaluate the effects and prognosis by biomechanical indexes from RSSCAN gait system and clinical scales. Our trial design is summarized in Figure 1. The study timeline and event schedule according to the Standard Protocol Items: Recommendations for Interventional Trials (SPIRIT) 2013 Statement^[20]^ are detailed in Figure 2.

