### Sample size

2.3

Out study is a preliminary clinical trial aiming to evaluate the feasibility of intradermal needle therapy for post-stroke hemiplegia recovery. Therefore, we did not determine sample size basing on statistical calculations.^[22]^ An alternative approach to estimate the sample sizes for pilot studies with 10 to 40 patients per group was adopted.^[23]^ Accordingly, to exceed the minimal number and combine with the actual situation, a total of 40 patients will be recruited in this research, 20 in each group. Assuming a 20% drop-out rate, we aimed to recruit 50 patients. Each group will require 25 initial participants.

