### Outcome measures

2.11

The participations will be examined at baseline, reexamined after 4-week treatment, and again at the end of 3 months’ follow-up. Data will be assessed by trained, certified assessors.

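### Within-group change is made part of the main analysis of the needle's effect, and the only test named for continuous outcomes would not be valid for before-after data

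*Protocol article*

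**What the plan says.** Section 2.18 (Statistical analysis) defines the main analysis in one sentence: "The main analysis will compare the changes in all outcome measurements of between-group or within-group to evaluate the effect of intradermal needle treatment". Between-group and within-group comparisons are joined as alternatives and share one stated purpose, evaluating the needle.

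For continuous variables the same section says that "Wilcoxon rank sum tests with no adjustment for multiple comparisons will be used for comparisons". No other test is named for them. Fisher's exact test appears only for the check of blinding, and no paired test appears anywhere in the article. The significance rule is a P "value of <.05 (2-sided) is considered to indicate statistical significance, with 95% confidence intervals".

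Section 2.11 says patients are "examined at baseline, reexamined after 4-week treatment, and again at the end of 3 months’ follow-up", so each patient contributes repeated values.

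Several other sections bear on what a within-group change can mean:

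- Sections 2.1 and 2.9 give conventional rehabilitation to both arms.
- Section 2.6 admits patients within 3 months of stroke.
- Section 2.10 allows other rehabilitation during follow-up, apart from further intradermal needling.

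**The concern.** There are two problems, and the first is the more serious.

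**Basis for inference.** A before-after change in the needle arm is the sum of recovery over time, conventional rehabilitation, any other treatment in follow-up, and any needle effect. The sham arm is there to remove all but the last. A sentence that lets within-group change evaluate the needle's effect allows a claim of benefit that makes no use of the sham arm. The exclusion wording in Section 2.7 about the 3 months after onset sits badly with Section 2.6, and the two need reconciling. The argument does not depend on that, because shared rehabilitation alone is enough to move both arms.

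**Test.** The rank-sum test assumes two independent samples. Baseline and later values from the same patients are paired. If the one named test is used for the within-group comparisons, its reference distribution is wrong. With positive before-after correlation it rejects too rarely.

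The two problems push in opposite directions. The test problem loses power. The risk of a false claim of benefit comes from the within-group wording.

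**Working it through.** **The plan's own figure.** Section 2.3 gives 20 per group and 40 in total, and says "Assuming a 20% drop-out rate, we aimed to recruit 50 patients". 40/(1 − 0.20) = 50 and 20/(1 − 0.20) = 25 per group, so the figure reproduces exactly. It fixes the arm size for what follows.

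**Inputs from the protocol.** 20 analysed per arm (Section 2.3), 1:1 allocation (Section 2.1), two-sided 0.05 (Section 2.18), and the same patients measured before and after (Section 2.11).

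**Assumed inputs.** The protocol gives no SD, effect size or before-after correlation. I assumed bivariate normal data with unit SD at both times, correlation ρ, and a mean shift in SD units. Results come from simulation with 3,000 to 4,000 runs per setting; a separate set of 20,000 runs at ρ = 0.5, 0.7 and 0.8 agreed closely.

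**Step 1: no needle effect, same recovery in both arms, 20 per arm.** Share of trials with P < 0.05:

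| Common recovery | ρ | Needle arm, signed-rank | Needle arm, rank-sum | Between groups, rank-sum on change |
|---|---|---|---|---|
| 0 | 0.5 | 0.050 | 0.007 | 0.052 |
| 0 | 0.8 | 0.051 | 0.000 | 0.055 |
| 0.3 SD | 0.5 | 0.229 | 0.071 | 0.050 |
| 0.3 SD | 0.8 | 0.499 | 0.028 | 0.047 |
| 0.5 SD | 0.5 | 0.540 | 0.277 | 0.048 |
| 0.5 SD | 0.8 | 0.907 | 0.229 | 0.051 |
| 0.8 SD | 0.5 | 0.914 | 0.714 | 0.056 |
| 0.8 SD | 0.8 | 1.000 | 0.810 | 0.048 |

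In the rows with recovery, the signed-rank test is correct that the arm has changed. The error lies in reading that change as an effect of the needle. The between-group test stays near 5% in every row; its Monte Carlo standard error is √(0.05 × 0.95/4000) = 0.003. Across the separate runs, the rank-sum figure at 0.5 SD spans about 22 to 28%.

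**Step 2: rank-sum against signed-rank on before-after data, 20 patients.**

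| ρ | Type I error, rank-sum | Type I error, signed-rank | Power at 0.5 SD, rank-sum | Power at 0.5 SD, signed-rank |
|---|---|---|---|---|
| 0.3 | 0.024 | 0.052 | 0.307 | 0.426 |
| 0.5 | 0.005 | 0.047 | 0.260 | 0.537 |
| 0.7 | 0.000 | 0.049 | 0.230 | 0.745 |
| 0.8 | 0.000 | 0.055 | 0.218 | 0.900 |

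The 20,000-run set gives type I errors for rank-sum of 0.0075, 0.0011 and 0.0003 at ρ = 0.5, 0.7 and 0.8, and power of 0.271, 0.240 and 0.215.

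**Step 3: why the direction is general.** An independent-samples statistic uses a variance for the difference proportional to 2, while the true variance is proportional to 2(1 − ρ). The effective critical value is therefore about 1.96/√(1 − ρ). At ρ = 0.5 this is 1.96/0.707 = 2.77, a two-sided tail of about 0.006, in line with the simulated 0.005 to 0.0075.

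**Sensitivity to arm size.** With all 25 per arm analysed and ρ from 0.5 to 0.8, type I error for rank-sum is 0.011 or less. Power at 0.5 SD is about 0.33 to 0.34 for rank-sum, against 0.65 to 0.96 for signed-rank. The picture is the same.

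**The case against.** The best defence has three parts.

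**The protocol never says that rank-sum is for before-after data.** The test is named in a different sentence from the one that mentions within-group comparisons. The stated object is change, and rank-sum on change scores between two randomised groups is valid. A condensed article may simply have left a paired test to a fuller document. This stands in part. A reader might infer that the plan definitely applies rank-sum to paired data and that its within-group P values will be wrong. The text supports only the conditional: they would be wrong if the one test named, without restriction, is used for them. The defence does not reach the first problem, because the purpose given to within-group change is stated outright.

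**The aim is comparative.** The Background asks whether add-on needling gives more effective recovery, the design is randomised and sham-controlled, and the between-group comparison is listed first and kept. This also stands. A reader might infer that the plan will declare success when the needle arm is significant and the sham arm is not, or that the randomised comparison has been replaced. No such rule is written. Any figure for how often the arms would disagree depends wholly on an assumed within-arm power, so none is offered here.

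**It is a pilot with no power calculation.** That lowers the stakes but does not remove them. Section 2.18 sets a significance threshold, and the Discussion speaks of possibly confirming whether the needle is effective and of a basis for further studies.

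**Conclusion.** The concern holds in a limited form. The protocol wrongly gives within-group change a part in evaluating the needle's effect. With no needle effect and a 0.5 SD recovery common to both arms, a significant change in the needle arm would appear in about 54 to 91% of trials by signed-rank, or 22 to 28% by rank-sum, against about 5% for the between-group comparison.

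Conditionally, if rank-sum is used on before-after data, its type I error falls below 1% instead of 5%. Its power at 0.5 SD is about 22 to 27%, where signed-rank would have 54 to 90%.

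These figures rest on 20 patients per arm, normal data, the assumed shift and an assumed correlation of 0.5 to 0.8. At a correlation of 0.3 the distortion is milder (type I error 2.4%). The direction holds for any positive correlation.

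The between-group rank-sum test on change scores is not in question. Because it is specified and valid on this point, and the trial is a pilot, this is something that should be fixed rather than a fault that undermines the trial.

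**What to change.** Amend Section 2.18, and any analysis plan that repeats it, in three places:

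1. Remove within-group comparison as a basis for judging effect, and state that the between-group comparison of change is the sole basis.
2. State that the rank-sum test applies to between-group comparisons.
3. State that within-group change is reported as descriptive. If it is tested, use a paired method: the Wilcoxon signed-rank test, or the mean change with its 95% confidence interval.

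This changes wording only. It needs no extra patients, visits or data, and the same measurements support it.
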